| 1. **If you are seeking access to data held under the CPRD Data Linkage Scheme, please select the source(s) of linked data being requested.**   **Hospital Episode Statistics**  **Cancer Registry Data***  **MINAP**  **ONS Mortality Data**  **Index of Multiple Deprivation/ Townsend Score**  **Mother Baby Link**  **Other: (please specify)**  ****Please note that applicants seeking access to cancer registry data must provide consent for publication of their study title and study institution on the UK Cancer Registry website. Please contact the CPRD Research Team on [contact] or email*** [***[contact]***](mailto:[contact]) ***to discuss this requirement further.*** |
| 1. **If you are seeking access to data held under the CPRD Data Linkage Scheme, have you already discussed your request with a member of the Research team?**   **Yes**  **No***  ****Please contact the CPRD Research Team on [contact] or email*** [***[contact]***](mailto:[contact]) ***to discuss your requirements before submitting your application.***  **Please list below the name of the person/s at the CPRD with whom you have discussed your request.** |
| 1. **Does this protocol involve requesting any additional information from GPs?**   **Yes***  **No x**  *** Please indicate what will be required:**  **Completion of questionnaires by the GP** Yes**  **No**  **Provision of anonymised records (e.g. hospital discharge summaries) Yes**  **No**  **Other (please describe)**  *** Any questionnaire for completion by GPs or other health care professional must be approved by ISAC before circulation for completion.*** |
| 1. **Does this protocol describe a purely observational study using CPRD data (this may include the review of anonymised free text)?**   **Yes* X No****  ***Yes: If you will be using data obtained from the CPRD Group, this study does not require separate ethics approval from an NHS Research Ethics Committee.***  **** No: You may need to seek separate ethics approval from an NHS Research Ethics Committee for this study. The ISAC will provide advice on whether this may be needed.*** |
| 1. **Does this study involve linking to patient *identifiable* data from other sources?**   **Yes**  **No X** |
| 1. **Does this study require contact with patients in order for them to complete a questionnaire?**   **Yes**  **No X**  ***N.B. Any questionnaire for completion by patients must be approved by ISAC before circulation for completion.*** |

**Protocol content checklist**

In order to help ensure that protocols submitted for review contain adequate information for protocol evaluation, ISAC have produced instructions on the content of protocols for research using CPRD data. These instructions are available on the CPRD website ([www.cprd.com/ISAC](http://www.cprd.com/ISAC)). All protocols using CPRD data which are submitted for review by ISAC must contain information on the areas detailed in the instructions. IF you do not feel that a specific area required by ISAC is relevant for your protocol, you will need to justify this decision to ISAC.

Applicants must complete the checklist below to confirm that the protocol being submitted includes all the areas required by ISAC, or to provide justification where a required area is not considered to be relevant for a specific protocol. Protocols will not be circulated to ISAC for review until the checklist has been completed by the applicant.

**Please note, your protocol will be returned to you if you do not complete this checklist, or if you answer ‘no’ and fail to include justification for the omission of any required area.**

|  | **Included in protocol?** | |  |
| --- | --- | --- | --- |
| **Required area** | **Yes** | **No** | **If no, reason for omission** |
| ***Lay Summary (max.200 words)*** | **x** |  |  |
| ***Background*** | **x** |  |  |
| ***Objective, specific aims and rationale*** | **x** |  |  |
| ***Study Type***  ***Descriptive***  ***Hypothesis Generating***  ***Hypothesis Testing*** | **x** |  |  |
| ***Study Design*** | **x** |  |  |
| ***Sample size/power calculation***  ***(Please provide justification of***  ***sample size in the protocol)*** | **x** |  |  |
| ***Study population***  ***(including estimate of expected number of***  ***relevant patients in the CPRD)*** | **x** |  |  |
| ***Selection of comparison group(s) or controls*** | **x** |  |  |
| ***Exposures, outcomes and covariates***  ***Exposures are clearly described***  ***Outcomes are clearly described*** | **x**  **x**  **x** |  |  |
| ***Data/ Statistical Analysis Plan***  ***There is plan for addressing confounding***  ***There is a plan for addressing missing data*** | **x**  **x**  **x** |  |  |
| ***Patient/ user group involvement †*** | **x** |  |  |
| ***Limitations of the study design, data sources***  ***and analytic methods*** | **x** |  |  |
| ***Plans for disseminating and communicating study results*** | **x** |  |  |

***† It is expected that many studies will benefit from the involvement of patient or user groups in their planning and refinement, and/or in the interpretation of the results and plans for further work. This is particularly, but not exclusively true of studies with interests in the impact on quality of life. Please indicate whether or not you intend to engage patients in any of the ways mentioned above.***

*ISAC strongly recommends that researchers using CPRD consider registering as a NRR data provider in order that others engaged in research within the UK can be made aware of current works. The* ***National Research Register (NRR)*** *is a register of ongoing and recently completed research projects funded by, or of interest to, the United Kingdom's National Health Service. Information on the NRR is available on* [*www.nrr.nhs.uk*](http://www.nrr.nhs.uk/) *.*

***Please Note: Registration with the NRR is entirely voluntary and will not replace information on ISAC approved protocols that are published in summary minutes or in the ISAC annual report****.*

**Summary of Research in plain English**

Parkinson’s disease (PD) is a progressive neurological disorder in which the brain is affected by a number of disease processes, one of which is inflammation. Recent *in vitro* and animal experiments suggest that a class of medication currently used to treat diabetes, glitazones (GTZs), may also be effective against the onset and progression of PD by reducing the inflammation in the brain associated with the disease process. GTZs have been used for >10 years in the United Kingdom to treat diabetes, and we believe that they may have slowed or prevented the onset of PD in people who have taken them. We will therefore look at a cohort of people with diabetes and compare people taking GTZs with people taking other diabetes treatments to see if those receiving a GTZ were less likely to develop PD. The findings of this study will help determine whether GTZs and drugs with similar actions may be useful in the treatment of PD.

**Aim**

To assess the effect of glitazones on the risk of Parkinson's disease.

**Objectives**

To estimate the rate ratio for Parkinson’s disease in people with diabetes, comparing individuals treated with glitazones to people treated with agents other than glitazones.

**Background & Rationale**

Parkinson’s disease is a degenerative neurological disease primarily characterised by nerve cell death in the substantia nigra and a consequent deficit in the amount of dopamine available in the central nervous system. People with PD gradually develop movement-related symptoms, including tremor, bradykinesia and rigidity. The pathophysiological causes of PD are complex, and are thought to involve oxidative stress, mitochondrial and proteasomal dysfunction and neuroinflammation (Jenner & Olanow, 2006). Neuroinflammation is partly mediated through microglia, which have been shown to proliferate and become chronically activated in PD. Microglia produce pro-inflammatory cytokines which are associated with tissue damage and are likely to partly explain the loss of dopaminergic neurons in PD (McGeer et al 1988, Forno 1992, Harada et al 1995, Liu & Hong 2003, Wyss-Coray & Mucke L 2002, Merrill & Benveniste 1996).

*In vitro* studies have shown that peroxisome proliferation-activated receptor gamma (PPARɣ agonist medications such as the antidiabetes GTZ drugs (pioglitazone and rosiglitazone) may have a neuroprotective effect through multiple anti-inflammatory properties, including an inhibitory effect on the activation of microglia (Hetzel et al 2003, Zafiriou et al 2005, Combs et al 2000). Pioglitazone specifically, has been shown to reduce inflammatory markers and offer near complete protection against dopaminergic neuronal loss in an animal model of PD (Sadeghian et al, 2012).

Current treatments for PD have focused on supplementing or improving the availability of dopamine, but such strategies are associated with diminishing returns and unpleasant side effects. So far, no effective treatments have been found to directly tackle the neurodegenerative aspect of the disease and further clinical exploration of these exciting findings with PPAR agonists is warranted. A very small clinical trial is currently exploring the use of pioglitazone to treat PD (Clinicaltrials.gov reg: NCT01280123), but will have very limited power. Since the late 1990’s GTZs have been prescribed in patients with diabetes. The Clinical Practice Research Datalink (CPRD) offers an ideal source of observational data to examine whether GTZ antidiabetic medications are protective against PD by determining their effect on PD onset in a large population. The results of this study will add substantially to the evidence base regarding the effects of GTZs on PD in clinical practice, and will be of great value when making decisions about where to focus resources for further clinical research.

**Study Type**

This is a hypothesis testing study

**Study design**

We will conduct a cohort study comparing the rate of PD diagnosis in people treated with GTZ antidiabetic drugs, compared with people being treated with non-GTZ antidiabetic drugs. This design will minimise confounding because both exposed and unexposed patients will have diabetes and will therefore have similar underlying health problems related to diabetes which may be associated with PD. Due to the cohort design we will also be able to examine whether any effect of GTZs changes over time.

**Study Population**

The study population will be drawn from the entire CPRD population with acceptable up to standard (UTS) follow up time. People will be selected for inclusion if they have received any prescription for a GTZ antidiabetic (code list in Appendix 1), with the first occurrence being at least 12 months after the patient’s start of UTS follow up. This is to increase the likelihood that we are studying new users of GTZs, which will be of importance when we assess any effect of treatment duration on PD risk. Eligibility will begin in 1999 when the first GTZ was launched. No age restrictions will be applied to eligibility; the mean age of type 2 diabetes diagnosis in a US population was ~ 46 years in 2000 (Koopman et al, 2005) and so we anticipate the age profile of patients receiving GTZ antidiabetics will be a little younger than the typical onset age for PD (over 50 year), making them an ideal group in which to study the long term effects of a potentially neuroprotective agent. Potential participants with any diagnosis of PD prior to their first GTZ prescription will be excluded. Users will be classified according to their diabetes treatment stage at the time the GTZ is started, as follows:

1. GTZ monotherapy, no prior oral anti-diabetic (OAD)
2. GTZ monotherapy, previous OAD discontinued
3. Combined OAD therapy, GTZ being taken with other OADs

A feasibility count shows there are ~43,000 incident GTZ users with at least 12 months prior UTS follow up. Follow up for the study analysis will begin at the first prescription for a GTZ and end at the earliest of last collection date for the practice, patient transfer out or death date.

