**Power Calculation**

Amongst the 43,000 GTZ exposed patients identified for the feasibility count, 144 were first diagnosed with PD after starting a GTZ. Using STATA 12, we estimate we will have 99% power to detect a 30% reduction in PD incidence amongst GTZ users, if we match each exposed patient to five unexposed. Power to detect a 25% and 20% reduction will be and 91% and 71% respectively. We believe an effect size of 25% would represent a clinically meaningful association, and may also be plausible, given the near complete protection identified in animal studies (Sadeghian et al, 2012).

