**Exposures, Outcomes and Covariates**

Exposure will be determined by prescribing records, using code lists for individual OADs. Code lists for GTZs can be found in Appendix 1. The index date for each patient will be their first prescribing event that qualifies them for study entry (e.g. first exposure to a GTZ)

The outcome for this study is the first recording of a PD diagnosis after the index date, as identified from clinical and referral records, using the Read code list in Appendix 2. PD due to known causes will be excluded based on the recording of codes presented in Appendix 2.

Covariates to be explored due to their possible association with PD and potential confounding nature will be:

- Smoking status determined using the additional clinical details file
- HRT use determined using prescribing records
- Head trauma as determined by Read code recording
- Age and sex will be accounted for through matching
- Calcium channel blocker use as determined by prescribing records: This exposure has been shown to reduce the incidence of PD (Becker et al, 2008).
- Diabetes itself has been shown to be possibly associated with PD (Wahlqvist et al, 2012). Length of time between diabetes diagnosis and index date, and HbA1c level at index date will be determined and explored for possible confounding properties. In addition, the effect of time updated HbA1c levels will be explored.
- Metformin has been suggested to also have a protective effect against PD (Wahlqvist et al, 2012). As a very commonly prescribed diabetes medication, this will be explored in detail as described below under “Statistical Analysis”.

Other covariates that have not been shown to be associated with PD will also be explored in case of possible confounding, and will include:

- Alcohol consumption
- Body mass index
- Calendar year

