**Statistical Analysis**

We will measure an incidence rate ratio for the association between GTZ use and incident PD using poisson regression, comparing patients exposed to GTZs with patients exposed to alternative treatments. The primary analysis will follow all patients from their index date until the earliest of a PD record, transfer out/death, or last collection date for the practice, and their exposure will remain as defined at the index date, regardless of any subsequent changes in therapy (analogous to an intention to treat analysis in a clinical trial). Secondary analyses will be as follows:

- Censoring follow up at end of GTZ therapy, defined as last prescription plus 90 days, followed by at least 180 days GTZ-free follow up time.
- Stratified analysis based on metformin and GTZ treatment status, to explore the individual and any additive effects of both treatments. Whilst we anticipate most patients will be exposed to metformin, we anticipate a sizeable population who will not receive metformin.
- We have chosen to measure the incidence of PD from the start of therapy with GTZs as the pre-clinical work to date suggests a fast onset of any protective effect. Whether this effect varies with exposure length will be assessed through a stratified analysis on length of follow up after starting GTZ therapy.
- Sensitivity analysis defining PD as a Readcode indicating PD plus at least 2 prescriptions for an anti-Parkinson’s drug, to reduce the likelihood of outcome misclassification. Although cases with little follow up beyond their diagnosis will be excluded, this approach will only reduce study power, but will reduce misclassification bias. The date of earliest recorded diagnosis will remain the date of the outcome.
- Sensitivity analysis to look separately at the effects of pioglitazone and rosiglitazone.
- Sensitivity analysis adjusting for all variables identified as potential confounders, in addition to those included in the forward stepwise modelling strategy (see below).

Adjustments for potential confounding will be made in a forward stepwise manner retaining variables in the model if they have a substantial impact on the estimated rate ratio (a change of 10% or more), and starting with variables that have the greatest effect on PD incidence in univariate analyses. All data management and analyses will be performed using Stata 12 (StataCorp, Texas).

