**Appendix 2: Codes used to identify Parkinson’s Disease**

Parkinson’s disease with no identified cause

| medcode | readterm |
| --- | --- |
| 1691 | paralysis agitans |
| 4321 | parkinson's disease |
| 8956 | parkinsonism with orthostatic hypotension |
| 9509 | [x]dementia in parkinson's disease |
| 10718 | o/e - parkinsonian tremor |
| 14912 | parkinson's disease nos |
| 16860 | o/e - parkinson gait |
| 17004 | o/e - parkinson posture |
| 53655 | o/e -parkinson flexion posture |
| 59824 | o/e-festination-parkinson gait |
| 86062 | [x]parkinsonism in diseases classified elsewhere |
| 96860 | cerebral degeneration in parkinson's disease |

Parkinsonism with identified causes

| medcode | readterm |
| --- | --- |
| 19478 | drug induced parkinsonism |
| 24001 | secondary parkinsonism due to other external agents |
| 26181 | secondary parkinsonism, unspecified |
| 33544 | parkinsonism secondary to drugs |
| 51105 | postencephalitic parkinsonism |
| 52589 | syphilitic parkinsonism |
| 72879 | [x]secondary parkinsonism, unspecified |
| 97170 | [x]other secondary parkinsonism |
| 100128 | vascular parkinsonism |

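### Existing Parkinson's disease is screened by diagnosis code alone, so a patient already on anti-Parkinson drugs but first coded after index counts as a new case

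*Protocol*

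**What the plan says.** Four parts of the Protocol bear on who is free of PD at the start of follow-up.

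- **Entry (Study Population).** "Potential participants with any diagnosis of PD prior to their first GTZ prescription will be excluded". This is the only stated screen for existing PD, and it works through recorded diagnoses.
- **Outcome (Exposures, Outcomes and Covariates).** "The outcome for this study is the first recording of a PD diagnosis after the index date, as identified from clinical and referral records". The same section adds: "PD due to known causes will be excluded based on the recording of codes presented in Appendix 2". It gives no date limit for those codes and does not say whether the person or only the event is removed.
- **Stricter case definition (Statistical Analysis).** "Sensitivity analysis defining PD as a Readcode indicating PD plus at least 2 prescriptions for an anti-Parkinson’s drug". No time window is given for the prescriptions. On dating the event: "The date of earliest recorded diagnosis will remain the date of the outcome". The text also accepts that cases with short follow-up after diagnosis will be lost under this definition.
- **Code lists (Appendix 2).** Idiopathic PD codes stand in one list and "Parkinsonism with identified causes" in a second, both under one heading for PD codes.

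No section uses anti-Parkinson prescriptions before index as an exclusion.

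**The concern.** The study asks whether starting a glitazone changes the rate of new PD, so everyone counted at risk should be free of PD at index. Someone already treated with anti-Parkinson drugs may well have the disease even though no PD code has yet been entered. If the first code arrives after index, the written rules admit this person and count the event. A drug started after the disease began cannot have prevented it.

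If such events are equally frequent in both arms, they dilute the rate ratio towards 1. If their frequency differs by arm, the bias can go either way. The planned stratification by length of follow-up could also be affected: if delayed codes cluster soon after index (an inference, not a statement in the Protocol), the early strata are diluted most, and a constant effect could look as if it grew with time.

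The Limitations section discusses false-positive PD diagnoses and adherence, but not disease already present at entry. A high positive predictive value does not help here, because a prevalent case is genuine PD with the wrong onset date.

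**Working it through.** **Step 1: follow one patient through the rules.** Anti-Parkinson drugs are prescribed before index; the first PD Read code is entered after index.

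- Entry: no PD diagnosis before index, so the patient is admitted.
- Primary outcome: the first PD code falls after index, so the event counts.
- Stricter definition, prescriptions counted at any time: the earlier ones suffice.
- Stricter definition, prescriptions counted only after the code: a patient already under treatment would normally continue and collect two more, so the event still counts, dated at the code.

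No rule in the Protocol stops this patient under either reading.

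**Step 2: reproduce the Protocol's power figures.** Inputs from Power Calculation: "Amongst the 43,000 GTZ exposed patients identified for the feasibility count, 144 were first diagnosed with PD after starting a GTZ", and one-to-five matching ("if we match each exposed patient to five unexposed"). Two-sided 5% significance is assumed, as none is stated. Let p1 = 144/43,000 = 0.00335 be the exposed proportion, p0 = p1/RR the unexposed proportion, and n0 = 5 × 43,000 = 215,000. Power = Φ[(p0 − p1 − 1.96·SE_pooled)/SE_unpooled].

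| True RR | Stated | Uncorrected | Continuity-corrected |
|---|---|---|---|
| 0.70 | 99% | 99.0% | 98.9% |
| 0.75 | 91% | 92.0% | 91.3% |
| 0.80 | 71% | 71.8% | 70.3% |

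The stated figures reproduce and are not in dispute. The uncorrected 92.0% is the reference below.

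**Step 3: size of the dilution.** The Protocol does not give the share of events that are prevalent disease, so it is assumed. Let s be the share among comparator events, with the same rate of such events in both arms and a true rate ratio of 0.75 for the rest:

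observed RR = 0.75 × (1 − s) + s.

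The exposed arm has fewer events in total, so the same rate makes up a larger share there, s / observed RR. The implied number among the 144 is 144 × s / observed RR. Power is recalculated with 144 exposed events held and p0 = p1 / observed RR.

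| s | Observed RR | Such events among the 144 | Power |
|---|---|---|---|
| 0 | 0.750 | 0 | 92.0% |
| 2% | 0.735 + 0.02 = 0.755 | 144 × 0.02/0.755 = 3.8 | 90.6% |
| 5% | 0.7125 + 0.05 = 0.7625 | 144 × 0.05/0.7625 = 9.4 | 88.3% |
| 10% | 0.675 + 0.10 = 0.775 | 144 × 0.10/0.775 = 18.6 | 83.6% |

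**Step 4: does removing these events cost more power than it saves?** Removing 2%, 5%, 10% or 20% of the 144 exposed events, and keeping RR at 0.75, gives power of 91.4%, 90.6%, 88.9% or 84.8%. In the last row of Step 3 the exposed share is 18.6/144 = 12.9%, so power after removal lies between 84.8% and 88.9%, against 83.6% if the events stay. Under these assumptions, removal does not reduce power overall.

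**The case against.** **The entry and outcome rules agree.** Both rest on diagnosis codes, and the stricter definition asks for a code together with drugs, never drugs alone. Anti-Parkinson drugs have other uses, so excluding on them is a trade-off. This stands: the plan does not contradict itself. It leaves a gap that evidence it already uses elsewhere could close.

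**The two prescriptions are probably meant to follow the code.** A reader might infer that prescriptions before index are accepted as confirmation. The remark that cases with little follow-up after diagnosis will be lost points the other way, since that follows only if the prescriptions are looked for after the diagnosis. The exact window may also belong in a statistical analysis plan. This stands too, but it does not close the gap, because a patient under treatment would normally have later prescriptions as well.

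**Secondary parkinsonism is dealt with.** A reader might infer that patients with a secondary-parkinsonism code before index certainly stay at risk. The Protocol does not support that: it excludes PD due to known causes without a time limit, which can be read as covering a code at any date. What remains is an ambiguity about whether an earlier code bars entry or only voids a later event.

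**The effect is small and probably rare.** Nothing in the Protocol suggests the pattern is common, and both groups need at least 12 months of prior follow-up in which a code could have appeared. With 144 exposed and 5 × 144/0.75 = 960 unexposed events, SE(log RR) = √(1/144 + 1/960) = 0.089, so the 95% interval runs from the estimate divided by 1.19 to the estimate multiplied by 1.19. A shift from 0.75 to 0.755–0.775 is 0.7% to 3.3%, well inside that. This stands as to size, but systematic bias that a query can remove is still worth removing.

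**Hospital-only prescribing is invisible.** Drugs that never reach the general practice record cannot be screened. That limits the repair without removing its value.

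**Conclusion.** The point holds in a limited form. Existing disease is screened by diagnosis code only, so a patient treated before index and coded after it enters as PD-free and counts as incident, and the stricter case definition would normally keep that patient. The route follows from the Protocol's text. The exception is continued treatment after the code, which is a reasonable expectation rather than a stated fact.

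The size is not known. On assumed shares of 2% to 10% of comparator events, equally frequent in both arms, a true rate ratio of 0.75 is seen as about 0.755 to 0.775, and power falls from 92.0% to between 90.6% and 83.6%. A reader might infer that the primary result would be materially distorted; the Protocol gives no figure to support that, and the illustrated shift is modest. The handling of secondary-parkinsonism codes before index is an ambiguity to settle, not an error shown. This is an inexpensive improvement that should be made, not a flaw that undermines the design.

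**What to change.** State one baseline rule in Study Population that applies to glitazone users and comparators at their own index dates. The present sentence is worded around the first glitazone prescription, so the new rule should name both groups.

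1. Exclude anyone with an anti-Parkinson drug prescription before the index date. If the team prefers to keep the primary cohort as it is, run this exclusion at minimum as a sensitivity analysis, and report how many patients and events it removes in each arm. Those counts would replace the assumed shares above.
2. State that a code from the second Appendix 2 list on or before the index date also bars entry.

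The cost is one further eligibility query. Prescribing records are already used for exposure and covariates, and the stricter case definition already needs a list of anti-Parkinson drugs. The drawback is that a few PD-free patients who take these drugs for other reasons are dropped.

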**Selection of Comparison Group**

Each GTZ exposed patient will be matched by age, sex, and practice with up to 5 patients receiving other oral treatment for diabetes (unexposed group). To reduce the possibility of confounding, we will only select patients who have also received oral antidiabetic treatments, thus reducing the difference in disease stage between GTZ users and non-users. GTZ prescribing has evolved during >10 years according to changes in treatment guidance and changes made to the licensed indication. Initially they were mostly used as second line combination treatment, but were subsequently also used at earlier stages of diabetes treatment. Rosiglitazone was eventually suspended due to cardiovascular safety concerns and pioglitazone use has waned due to concerns over the risk of bladder cancer. To be considered for inclusion, only patients present in the database from 1999 onwards and with at least 12 months UTS follow up prior to prescribing events that trigger eligibility will be included. For instance a patient could be matched to a GTZ user in category 1) above if they had never received an OAD before 1999 and began taking a sulphonylurea with no other OAD after at least 12 months UTS follow up. Follow up for the unexposed will begin at the first prescribing event that makes them eligible for inclusion.

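### The prior-PD exclusion is tied to the first glitazone prescription and so does not reach comparators; applied literally with the outcome wording, it would bias the rate ratio towards protection

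*Protocol*

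**What the plan says.** Four places in the protocol bear on this.

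- **Study Population**, in the paragraph that selects glitazone (GTZ) users: "Potential participants with any diagnosis of PD prior to their first GTZ prescription will be excluded". No other rule in the protocol excludes prior PD.
- **Selection of Comparison Group**: comparators are matched on age, sex and practice, take other oral diabetes treatment, and are limited to "only patients present in the database from 1999 onwards and with at least 12 months UTS follow up prior to prescribing events that trigger eligibility". Their time at risk starts as follows: "Follow up for the unexposed will begin at the first prescribing event that makes them eligible for inclusion". Nothing here requires them to be free of PD.
- **Exposures, Outcomes and Covariates**: "The index date for each patient will be their first prescribing event that qualifies them for study entry", so every patient in both groups has an index date. The outcome is then set: "The outcome for this study is the first recording of a PD diagnosis after the index date". The section also excludes PD due to known causes, which concerns the type of parkinsonism and not its timing.
- **Statistical Analysis**: "We will measure an incidence rate ratio for the association between GTZ use and incident PD using poisson regression". This states the intended target but adds no eligibility rule.

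**The concern.** The reference date of the exclusion exists in one group only. A GTZ user with PD before the first GTZ prescription is removed. A never-user with the same history passes every stated eligibility rule. If the outcome is then read as the first code after index, and not the first ever, that comparator's next PD code is an event.

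The error would raise the unexposed rate and leave the exposed rate untouched, so it favours the study hypothesis. The Limitations section does not cover it: outcome misclassification is described there as probably non-differential and biasing towards the null, whereas this would be differential and bias away from it. If established cases are re-coded soon after index, the excess would also fall early in follow-up. That could look like the rapid protective effect the protocol anticipates, and it could distort the analysis stratified by length of follow-up.

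**Working it through.** **Inputs from the protocol (Power Calculation).** "Amongst the 43,000 GTZ exposed patients identified for the feasibility count, 144 were first diagnosed with PD after starting a GTZ". This gives p = 144/43,000 = 0.335%. With five comparators per user there are at most 5 × 43,000 = 215,000 comparators.

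**Reproducing the stated power.** A two-proportion test with exposed risk p, unexposed risk p/RR, 1:5 allocation and two-sided alpha of 0.05 (alpha is not stated and is assumed here) gives 99.0%, 92.0% and 71.8% for reductions of 30%, 25% and 20%. With a continuity correction the values are 98.9%, 91.3% and 70.3%. The protocol states 99%, 91% and 71%, so its figures reproduce. They rest on first diagnoses after starting a GTZ, that is, on incident events.

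**Bias under the literal rules.** Assume a true rate ratio of 1 and similar follow-up in both groups. Let prev be the share of comparators with PD before index, and q the share of those who have a further PD code after index. Neither is given in the protocol; both are assumptions. Then

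observed RR = p / [p(1 − prev) + prev × q]

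With 215,000 comparators and no contamination, 5 × 144 = 720 comparator events are expected. The false events number 215,000 × prev × q.

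| prev | q | False events | All comparator events | Observed RR |
|---|---|---|---|---|
| 0.1% | 10% | 22 | 719.3 + 21.5 = 740.8 | 720/740.8 = 0.97 |
| 0.1% | 50% | 108 | 719.3 + 107.5 = 826.8 | 720/826.8 = 0.87 |
| 0.25% | 50% | 269 | 718.2 + 268.8 = 987.0 | 720/987.0 = 0.73 |
| 0.3% | 100% | 645 | 717.8 + 645.0 = 1,362.8 | 720/1,362.8 = 0.53 |

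For the second row the approximate 95% interval is 0.73 to 1.04, which includes 1.

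**Threshold without choosing prev and q separately.** Ignoring the negligible factor (1 − prev), a given spurious RR needs prev × q = p/RR − p.

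- RR 0.90: p/9 = 0.037%, or 80 false events.
- RR 0.80: p/4 = 0.084%, or 180 false events.
- RR 0.75: p/3 = 0.112%, or 240 false events.

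The last line is the 25% reduction that the protocol calls clinically meaningful.

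**After the fix.** prev = 0, so the ratio under no effect is 720/720 = 1.00.

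**The case against.** The best defence is that first-ever PD was meant throughout. The Statistical Analysis section names incident PD as the outcome. The feasibility count is of patients first diagnosed after starting a GTZ. The lay summary and rationale speak of developing PD and of its onset. The outcome sentence itself can be read as the first recording ever, which must fall after index. The sensitivity analysis requiring two anti-Parkinson prescriptions says that the outcome keeps the date of the earliest recorded diagnosis, which implies that the main analysis uses that date too. On that reading a comparator with pre-index PD could not supply an event.

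This stands as strong evidence of intent. It does not supply a rule: no sentence removes such a comparator from the cohort, and an analyst who codes the stated eligibility criteria would filter GTZ users only. Nor does the sensitivity analysis clearly cure the problem. A treated prevalent case meets its definition, and the protocol does not say what to do when the earliest diagnosis precedes the start of follow-up.

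A second objection concerns size, and it also stands. Prevalence and re-recording are not in the protocol. Comparators are age-matched to users whom the protocol expects to be somewhat younger than the typical age at PD onset, which argues against assuming a high prevalence.

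**Conclusion.** The defect is in the rules as written: the prior-PD exclusion has a reference date in one group only, the comparator rules have no counterpart, and the outcome wording does not close the gap. If the rules are applied literally to never-users, the bias is always towards apparent protection.

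A reader might go further and infer that the study will count prevalent PD as incident, and that the resulting bias matches or exceeds the 20% to 30% effects it is powered for. The documents support neither inference. The references to incident PD and to the earliest recorded diagnosis point the other way on intent. The size depends on two quantities the protocol does not give, and over the assumptions shown the spurious ratio runs from about 0.97 to about 0.53. The milder cases, reductions of 3% and 13%, fall short of 20%.

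The case for correcting the text is that a small contamination is enough: about 0.11% of comparators with re-coded pre-index PD would turn no effect into a ratio of 0.75. The power figures are not in question.

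**What to change.** Anchor the exclusion to the index date that the protocol already defines for every patient: exclude any patient, exposed or unexposed, with a PD diagnosis recorded on or before their own index date. Define the outcome as the first-ever PD record, occurring after the index date. The same filter then governs the sensitivity analysis with anti-Parkinson prescriptions, so no outcome date can precede follow-up.

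The cost is two sentences, one extraction filter and a small loss of comparators, whose number depends on the unknown prevalence. The stated power does not change, because it already assumes incident events. If first-ever PD was intended all along, the change only writes that down. How pre-index codes for parkinsonism with identified causes should be handled is a separate matter and is not part of this correction.
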